## Abstract

**Background:**

Pelvic Girdle Pain (PGP) is an important cause of disability and economic cost worldwide. There is a need for effective preventative and management strategies. Emerging studies measure a variety of outcomes rendering synthesis and translation to clinical practice difficult. A Core Outcome Set (COS) can address this problem by ensuring that data are relevant, useful and usable for making well-informed healthcare choices. The aim of this study is to develop a consensus-based PGP-COS, including agreement on methods (e.g. instruments) for measuring the construct outcomes in the COS for use in research and clinical practice. Furthermore, as there is uncertainty as to whether incorporating stakeholder interviews in addition to conducting a systematic review to determine an initial list of outcomes for the Delphi survey, or, whether using different rating scales in a Delphi survey impacts on the final COS, we propose to embed two methodological studies within the PGP-COS development process to address these questions.

**Methods:**

The PGP-COS study will include five phases: (1) A systematic review of the literature and semi-structured interviews with 15 patients (three countries) to form the initial list of outcomes for the Delphi survey; (2) A 3-round Delphi including patients, clinicians, researchers and service providers; (3) A systematic review of methods for measuring the outcomes in the preliminary PGP-COS identified in the Delphi survey; (4) A face-to-face consensus meeting to agree on the final PGP-COS and methods for measuring the COS; (5) Global dissemination.

To address the methodological questions, we will assess the number and type of outcomes, in the final PGP-COS, that were exclusively derived from the interviews. Secondly, we will randomise Delphi survey participants to either a 5-point or 9-point importance rating scale, and examine potential differences in ‘important’ ratings between the groups.

**Discussion:**

There is currently no COS for measuring/monitoring PGP in trials and clinical practice. A PGP-COS will ensure that relevant outcomes are measured using appropriate measurement instruments for patients with PGP globally.

**Core outcome set registration:**

This PGP-COS was registered with COMET (Core Outcome Measures for Effectiveness Trials) in January 2017 (http://www.comet-initiative.org/studies/details/958).

**Electronic supplementary material:**

The online version of this article (10.1186/s12874-018-0624-5) contains supplementary material, which is available to authorized users.

## Background

Low back pain is a leading cause of Years Lived with Disability (YLD) [1], is the sixth largest contributor to Disability Adjusted Life Years (DALYs) [2] and is associated with high costs of healthcare utilisation and absenteeism from work. Pelvic Girdle Pain (PGP) has sometimes been considered one of the main subgroups of low back pain; however, currently experts agree that PGP has distinct symptomatology and that differentiation between low back pain from lumbar origin and PGP is essential for appropriate management [3]. Moreover, PGP may include symphysis pubis pain, which cannot be classified as low back pain. Subsequently, PGP is a distinct condition, and treatment, examination and outcomes should be studied taking this into account to increase our understanding of PGP.

Pelvic Girdle Pain can be related to blunt or repetitive trauma, osteoarthritis or arthritis, and can as such affect both men and women. In most cases there is no clear explanation for the onset of PGP, but it is particularly common during pregnancy and most studies have been conducted on pregnant or postpartum women. Very little is known about other PGP groups due to a lack of studies. Pelvic Girdle Pain affects around half to two thirds of women at some point during pregnancy [4, 5] and 8.5% continue to have significant symptoms two years postpartum [6]. It is also the number one cause of sick leave during pregnancy [7–9] with large economic, social and psychological impact on individual families and the wider society. There is an urgent need for effective preventative and management strategies to address this personal and societal burden for women in fertile age [3, 10]. However, emerging studies measure a variety of outcomes and measure the same outcomes by different methods [5, 10], rendering synthesis and translation to clinical practice difficult and sometimes impossible.

A core outcome set (COS) is a standardised set of outcomes which should be measured and reported worldwide, as a minimum, in all studies for a specific health area/condition [11], and many COS across different healthcare fields have been developed, for example, COS in non-specific low-back pain complex regional pain syndrome [12, 13]. A COS allows for findings to be combined, compared and contrasted, reduces potential for reporting bias, and ensures that the data are useful and usable, which is essential for making well-informed healthcare choices. There was no registered or published COS for PGP. We registered this PGP-COS with COMET (Core Outcome Measures for Effectiveness Trials) in January 2017 (http://www.comet-initiative.org/studies/details/958). COMET is an initiative that focuses on the development and application of COS. They aim to collate relevant resources in the COMET database, have published the COMET handbook on developing COS and provide an online registry for COS projects to promote transparent COS development (see http://www.comet-initiative.org/).

## Methods/design

### Aim

To describe the protocol to develop a consensus-based PGP-COS for use in research and clinical practice so as to promote the health and well-being of women with PGP globally, by ensuring consistent and relevant outcome measurement and reporting in any prevention and management strategy.

## Objectives

To collate a list of reported outcomes from a systematic review of the literature of studies on PGP and from patient interviews for use in a Delphi survey;To develop consensus on a preliminary PGP-COS, using the list of outcomes from Objective 1, via a 3-round international electronic Delphi survey;To synthesise the evidence on the available outcome measurement instruments for measuring the construct outcomes (e.g. pain) in the preliminary PGP-COS;Using the preliminary PGP-COS (Objective 2), develop a final PGP-COS for use in all future studies on PGP, and in clinical practice, including how to measure the outcomes in the COS, via an international face-to-face consensus meeting with key stakeholders;To disseminate and promote the implementation of the COS to key stakeholders internationally;

In addition, we have two methodological objectives:6.To determine if including patient interviews in addition to a systematic review to identify the initial list of outcomes influences the final COS;7.To evaluate any differences in using a 9-point versus a 5-point rating scale in the Delphi survey, in terms of its impact on the number of ‘important’ ratings received for each outcome in each round of the survey and on the final PGP-COS.

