### Phase two: Online international Delphi survey

A sequential 3-round electronic, international Delphi study will be conducted including key stakeholders (patients/public, healthcare professionals, researchers, and service providers) to produce a preliminary PGP-COS. We will use online SurveyMonkey software to conduct the survey (www.surveymonkey.com). Each round will remain open for 14 days and a reminder email will be sent out four working days before closure. The data from each round will be analysed and presented to participants in the subsequent round. We will assess attrition rates for each round for all stakeholder groups.

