#### Participants

We will invite people from all stakeholder groups, aiming for approximately 40 experts from each stakeholder group (patients, clinicians, researchers, service providers/policy makers) to participate (which will provide 20 people randomised to each scale; see methodological study 2). We will recruit participants for the Delphi survey through professional organisations, electronic discussion lists, and patient organisations. We will also encourage snowball sampling, asking participants to forward the invitation appropriately.

Eligible participants will be: (a) Researchers who are actively involved in research related to PGP/lumbopelvic pain and have at least one peer-reviewed publication on the topic; (b) Clinicians, currently treating patients with PGP (including chiropractors, physiotherapists, osteopaths, orthopaedic surgeons etc.); (c) Patients with PGP; (d) Policy-makers, involved in formulating policies related to the management of musculoskeletal conditions including PGP; and (e) Service providers of services for musculoskeletal conditions including PGP. Participants must be able to read and understand English in order to participate.

#### Round 1

Round 1 will collect demographic data including nationality, age, gender, stakeholder group and profession. Participants will rate the importance of each listed outcome. Outcomes will be rated in each round on a 9-point scale [16] or on a 5-point scale (see methodological study 2 below). Participants will also be given the opportunity to add any additional outcomes not already in the list that they think are important. All outcomes from round 1 will be forwarded to round 2.

#### Round 2

Participants who responded to round 1 will be presented with feedback (descriptive statistics) on their own and others’ scores from round 1 and asked to rescore all outcomes and score new outcomes added in round 1. The reason for providing feedback from the previous round to participants is to increase the degree of consensus [14]. Participants will rate outcomes using the same scale they used in round 1. Outcomes from round 2 will be forwarded to round 3 where 70% or more of participants score the outcome as ‘important’ (7 or more on the 9-point scale, or 4 or more on the 5-point scale), and less than 15% of participants scoring an outcome as ‘not important’ (3 or less on the 9-point scale, or 2 or less on the 5-point scale) (Tables 2 and 3).

**Table 2 Tab2:** The 9-point rating scale

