#### Methodological study 2: Different scales to rate outcome importance

The 9-point scale, whereby a score of 1–3 means limited importance, 4–6 means maybe important but not critical, and 7–9 means critically important, is commonly used in Delphi surveys for COS development [14] and is based on the recommendations of the Grading of Recommendations Assessment, Development and Evaluation (GRADE) working group to assess the importance of evidence. However, other scales have been used [24, 25], and comments from some participants in round 1 of an in-progress recent Delphi survey described the 9-points scale as somewhat confusing and that a smaller scale might have been more user friendly [26]. Currently, no studies have examined the impact of using different likert scales on the final COS. We aim to compare the use of a 9-point scale (Table 2) versus a 5-point scale (Table 3). Participants of the Delphi survey, when clicking on the link to the survey, will be randomised to completing the survey using either a 9-point or 5-point scale. Specific software has been developed to enable this [27]. We will compare the two groups, with regards to the following outcomes: (a) the proportion of outcomes rated as ‘important’ (7 or above on 9-point scale, and 4 or 5 on 5-point scale) in each round and any differences between the scales, in the outcomes that are included in the preliminary COS after round 3. We will use z-scores to test the differences in proportions between the groups, and calculate overall mean scale differences on each outcome to assess differences. Recognising that differences can occur due to chance, and allowing for a 20% possibility of this, we would anticipate balance between the groups due to random allocation and thus similarity in overall scale scores for each outcome by population group. We will also ask participants to rate the ‘ease of use’ of the rating scale to assess utility.

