### Sample size

In phase 1, for the qualitative interviews, a purposive sample of 15 patients will be interviewed (5 in Ireland, 5 in Mexico, and 5 in Sweden). There is no consensus on methods for determining the sample size in qualitative research. The concept of data saturation is sometimes used, which is defined as the point when no new codes arise; however, this has been contested because the decision to cease recruitment remains subjective [33]. Subsequently, we based the sample size on previous COS development projects and guidance [16, 34].

For phase 2, limited guidance is available regarding methodological considerations using the Delphi technique [18] and sample size is not based on power calculation [14]. Subsequently, we based our sample size on existing COS development projects in the field [35]. Response rates in Delphi studies for COS can be low [29], hence we will invite sufficient people from all stakeholder groups, aiming for approximately 40 experts from each stakeholder group (patients, clinicians, researchers, service providers/policy makers) to participate (which will provide 20 people randomised to each scale; see methodological study 2).

In phase 5, a purposive sample of 20 experts will form the consensus panel. The COMET handbook does not specify a recommended number of participants to attend the consensus meeting [14] and sample size for this project has been determined to ensure that it is large enough to include multiple stakeholders (at least two for each stakeholder group) from different countries, ensuring adequate international representation, while minimizing costs.

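### Objective 7 promises the rating scale's effect on the final COS and in every round, but no randomised contrast on the final COS exists, and only round 1 is free of feedback, filtering and drop-out

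*Protocol article*

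**What the plan says.** Objective 7 (Objectives) sets out to evaluate the two scales by their impact on the number of important "ratings received for each outcome in each round of the survey and on the final PGP-COS".

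The relevant design features are these:

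- **Randomisation.** Each participant is allocated once, on opening the survey link, and keeps the same scale in later rounds (Methodological study 2; Round 2).
- **Numbers.** The target is "aiming for approximately 40 experts from each stakeholder group (patients, clinicians, researchers, service providers/policy makers) to participate". On the split between the scales, the Sample size section states "which will provide 20 people randomised to each scale; see methodological study 2". It notes as well that "sample size is not based on power calculation".
- **Round 1 to round 2.** Every outcome goes forward. Round-1 responders "will be presented with feedback (descriptive statistics) on their own and others" participants' scores before rescoring, and the stated purpose is to increase consensus. The article does not say whether the others are raters on the same scale or on both.
- **Round 2 to round 3.** "Outcomes from round 2 will be forwarded to round 3 where 70% or more of participants score the outcome as" important and under 15% score it not important. The cut-offs for both scales are given side by side within one rule. The same rule after round 3 defines one preliminary COS.
- **Analysis.** Methodological study 2 uses z-tests of proportions in each round and looks for differences between the scales "in the outcomes that are included in the preliminary COS after round 3".
- **Final COS.** One face-to-face panel of about 20 people decides, with a 70% vote (Phase four).
- **Attrition.** "We will assess attrition rates for each round for all stakeholder groups".

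**The concern.** The objective and the analysis meant to serve it do not match. The objective names the final COS; the analysis section stops at the preliminary COS. The meeting yields a single final list, so nothing on it can be compared by randomised scale.

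The later-round comparisons also differ in kind from the round-1 comparison. Round-1 ratings come from everyone randomised who answers, on an unfiltered list, before anyone has seen another person's score. In round 2 the ratings respond to feedback and come only from round-1 responders. In round 3 the list has also been filtered on the very quantity being compared. Yet the plan applies the same z-test in each round, as if the three had equal standing.

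Methodological study 2 says that no studies have examined how different scales affect the final COS, so readers may rely on this result. A finding of no difference after round 3 could come partly from the filter or from feedback, and a significant difference in round 2 or 3 could come from raters on one scale following a shared signal.

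**Working it through.** **1. The plan's own figure.** 40 per stakeholder group × 1/2 = 20 per scale per group, as stated. Four groups give 160 in total and 80 per scale. The article gives no alpha, power or effect size, so everything below that uses them is an assumption.

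**2. Final COS.** Objective 7 names the final COS. Methodological study 2 analyses the preliminary COS. Phase four produces one final list from one vote with no scale arms. One list gives no between-scale contrast; this step needs no assumption.

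**3. The filter after round 2, if one rule covers both scales.** In equal arms, 60% and 78% combine to (60 + 78)/2 = 69%, below 70%, so the outcome is dropped although it passed on one scale.

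For probabilities, take 80 per scale, true support of 65% and 75%, and only the 70% part of the rule. Let X and Y be the binomial counts of important ratings. A scale passes an outcome at 0.7 × 80 = 56 or more; the combined rule passes it at X + Y of 112 or more.

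| Event | Probability |
|---|---|
| Passes on the 65% scale | 0.21 |
| Passes on the 75% scale | 0.88 |
| Passes combined | 0.54 |
| The scales disagree | 0.72 |
| Passes on one scale only and is dropped combined | 0.36 |

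The last row is the share that a round-3 comparison cannot show.

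**4. Feedback within a scale, no true scale effect.** Suppose a share w of raters redraw their rating from the proportion observed on their own scale in round 1, and the rest keep theirs. The round-2 proportion then has variance

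p(1−p)/n × [1 + w(2−w)],

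where the first term is carried over from round 1 and the second comes from the redraws. The z-test uses p(1−p)/n alone, so its true two-sided level is 2 × [1 − Φ(1.96/√(1 + 2w − w²))].

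| w | 1 + 2w − w² | 1.96/√ | True level |
|---|---|---|---|
| 0.2 | 1.36 | 1.68 | 9% |
| 0.3 | 1.51 | 1.60 | 11% |
| 0.5 | 1.75 | 1.48 | 14% |

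Simulation at p = 0.7 and n = 80 agrees with these levels, and gives about 5% when feedback is shared across scales.

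**5. Feedback across scales, true effect present.** If raters move a share w of the way to the combined result, the difference becomes (1−w) times its previous value in each round. With w = 0.25, 20 points becomes 15, then 11; with w = 0.5, it becomes 10, then 5. At 80 per scale and two-sided 5%, power falls from 79% to 54% and 34% in the first case, and to 28% and 10% in the second. A milder model, with raters moving toward the fed-back mean, takes an 11.1-point difference only to 10.6, 10.3 or 8.9 points in round 2 for w = 0.2, 0.3 or 0.5. The direction is the same in both models; the size is not.

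**6. What round 1 can detect.** With proportions centred on 70% and 80 per scale, power is Φ{[d − 1.96√(2 × 0.7 × 0.3/80)] / √[(p₁q₁ + p₂q₂)/80]}: 28% for d = 10 points, 54% for 15 and 79% for 20.

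**The case against.** The strongest case against is that the article already contains most of what is needed.

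- **Combining the scales is inferred.** The rule refers only to participants, and the planned comparison of what enters the preliminary COS implies some tabulation by scale. This stands as a limit: a single combined rule is the natural reading of one round-3 list and one preliminary COS, but it is not stated. Tabulating by scale after round 3 would not bring back outcomes already removed.
- **Round 1 is already compared, and round 2 rescores the full list.** Correct. Disagreements between the scales are recorded twice before any filter, so only the round-3 comparison is truncated.
- **Feedback belongs to any Delphi.** A reader might infer that rounds 2-3 are worthless or that their differences are biased. The article does not support that. With feedback within a scale, the later contrast still targets the effect of running a Delphi on that scale; what fails is the z-test's variance, because raters sharing feedback are not independent.
- **Drop-out.** A reader might infer that inviting only responders, with attrition planned by stakeholder group, already biases the comparison. It does so only if loss depends on both scale and rating, and nothing in the article shows this. Attrition by scale and the form of feedback are details an article may leave to a fuller document.
- **The size of the filter effect.** A reader might infer that about half of all disagreements would be lost. Simulated support centred on the 70% cut-off (Beta(7,3)) does give 49-55%, but that share is largest when the scales do not differ at all, so much of it is chance near the threshold. With support placed higher (Beta(9,1.5)) it is 32-47%.
- **Tracing to the final COS.** One can describe which final outcomes met the rule on each scale. That is fair, but it is description, not a randomised effect.

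**Conclusion.** The point holds within these limits. That no randomised contrast on the final COS exists follows from the text alone, as does the mismatch between objective 7 and methodological study 2. Truncation of the after-round-3 comparison holds if one rule is applied over both scales; its size (36% in the 65% versus 75% example) depends on assumed support and 80 raters per scale. That the round 2-3 z-tests lack the properties of a clean randomised comparison holds under either form of feedback: they are diluted if feedback crosses scales, and run at about 9-14% instead of 5% in round 2 if it stays within a scale and 20-50% of raters follow it. Those weights are assumptions, and other movement models give other sizes. Round 1 is the only comparison free of feedback, filtering and drop-out between rounds. The selection of the COS itself is not put in doubt.

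**What to change.** 1. Name round 1, with all randomised raters, as the primary comparison for objective 7. Label rounds 2 and 3 descriptive and draw no nominal-level z-test conclusions from them. Outcomes suggested in round 1 are first scored in round 2 and can be listed separately.
2. Apply the 70%/15% rule separately within each scale to the full-list ratings of rounds 1 and 2, as well as to round 3. Report the lists and their agreement. Leave the rule that selects outcomes for the COS unchanged.
3. In objective 7, replace final PGP-COS by preliminary PGP-COS, and describe any tracing of outcomes to the final COS as descriptive.

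Tabulating attrition by scale would be a useful addition, though its absence is not an error.

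The cost is a change of wording, a few more tables and no confirmatory test in rounds 2-3. No extra participants are needed and the survey itself does not change. The primary comparison keeps the limited power shown above, so a round-1 result of no difference should be reported with its confidence interval.

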### Design

A consensus Delphi survey and face-to-face meeting will be used to identify and agree on a PGP-COS, informed by comprehensive systematic reviews of outcomes and outcomes measurement instruments for PGP. Figure 1 provides an overview of the study phases. The PGP-COS project plan was registered with COMET and is publically available to avoid duplication (http://www.comet-initiative.org/studies/details/958). This protocol was developed in accordance with the COMET handbook [14] and COSMIN (Consensus-based Standards for the selection of health Measurement Instruments) guidance [15]. The study steering committee will include researchers, clinicians, methodologists and at least one patient representative, and will meet quarterly to discuss progress and monitor the conduct of the study. In case of any significant changes to this protocol in future, these will be communicated to the ethics committee, the journal and the funders.

